### 2.2. Study Design

This study will be conducted across four medical and rehabilitation centers and follow a randomized, double-blind, parallel-group design to assess the impact of a community-based resistance training program for stroke survivors with sarcopenia. A total of 120 participants will be randomly assigned in a 1:1 ratio to either the intervention group, which will engage in structured resistance training, or the control group, which will continue their routine activities without a structured exercise program. To ensure unbiased results, assessors conducting evaluations will remain blinded to group assignments throughout the study.

The study will be conducted at (1) the National Rehabilitation Center, (2) Bucheon SM Hospital, (3) Korea University Anam Hospital, and (4) the National Health Insurance Service Ilsan Hospital. Participants will be recruited from outpatient rehabilitation programs at these institutions. Eligibility will be confirmed through a pre-screening process, followed by an informed consent procedure to ensure that participants fully understand the study objectives and methodology.

Once enrolled, participants will undergo baseline assessments before randomization. The intervention group will participate in a high-speed power training program designed to enhance muscle strength, functional performance, and mobility. The program will be conducted twice a week for 8 weeks, with each session lasting 60 min and incorporating progressive resistance exercises. Meanwhile, the control group will maintain their regular daily activities without any structured exercise intervention while continuing to receive standard medical care.

Outcome assessments will be conducted at two key time points: before the intervention (baseline) and after completing the 8-week program (post-intervention). The overall study procedure, including recruitment, group allocation, intervention, and assessments, is illustrated in Figure 1. The outcome measures will include muscle strength, physical function, body composition, and cardiopulmonary fitness. The collected data will undergo statistical analysis to evaluate the effectiveness of the resistance training program in mitigating sarcopenia-related functional decline among stroke survivors.

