### 2.3. Randomization

This study employs a computer-generated, stratified block randomization method to ensure a balanced allocation of participants across study groups. After completing baseline assessments, eligible participants will be randomly assigned in a 1:1 ratio to either the intervention group (high-speed power training program) or the control group (standard care). To maintain allocation concealment, the randomization process will be conducted independently by a statistician who is not involved in participant recruitment, assessment, or intervention delivery.

Randomization will be stratified by study site and baseline functional status to ensure that both groups have comparable distributions of key characteristics. To achieve this, four to six block sizes will be used, and assignments will be sealed in opaque, consecutively numbered envelopes prepared by an independent research assistant. These envelopes will be opened only after the participant is enrolled and their baseline assessment is completed.

To minimize bias, this study follows a double-blind design, where participants and outcome assessors remain unaware of group assignments throughout the study period. Only the exercise specialists administering the intervention will have access to group allocation. Participants will be instructed not to disclose their group assignment to assessors during follow-up evaluations.

This randomization strategy ensures that the study groups remain well balanced, reducing the risk of selection bias and enhancing the reliability of the study findings.

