### 2.4. Randomization and Blinding

This study employs a stratified block randomization method to ensure a balanced allocation of participants across the intervention and control groups. Randomization will be stratified by study site and baseline functional status, with block sizes of four to six, to minimize imbalance between groups. An independent statistician who is not involved in participant recruitment, assessment, or intervention delivery will generate the random allocation sequence using computerized randomization software. Group assignments will be sealed in opaque, consecutively numbered envelopes, which will only be opened after participant enrollment and baseline assessment.

To maintain blinding, this study follows a double-blind design, where both participants and outcome assessors will remain unaware of group assignments throughout the study. Only the exercise specialists delivering the intervention will have access to group allocation. Participants will be instructed not to disclose their group assignment during follow-up evaluations to prevent bias.

Additionally, data analysts will be blinded to group assignments during statistical analysis to ensure the unbiased interpretation of results. This randomization and blinding protocol is designed to reduce selection bias, measurement bias, and potential confounding factors, ultimately enhancing the validity and reliability of the study findings.

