### 2.9. Statistical Analysis

The statistical analysis for this study will be conducted using IBM SPSS Statistics (version 26.0; IBM Corp., Armonk, NY, USA). Before the trial, a sample size calculation was performed using G*Power (version 3.1.2), assuming an effect size of 0.5, a significance level (α) of 0.05, and a statistical power of 80% (1–β). The effect size (Cohen’s d = 0.5) was selected based on prior studies showing the moderate-to-large effects of high-velocity or multicomponent resistance training in stroke or sarcopenic populations [19,20]. An anticipated attrition rate of 20% was assumed, consistent with previous 8–12-week intervention studies in community-dwelling stroke survivors [21], resulting in an adjusted target of 120 participants. Based on these assumptions and accounting for possible attrition, a total of 120 participants will be recruited—30 individuals from each of the four participating institutions.

Descriptive statistics will be computed to characterize the participants and evaluate baseline equivalence between the intervention and control groups. Categorical data will be presented as frequencies and percentages, while continuous data will be summarized as means with standard deviations or medians with interquartile ranges, depending on the distribution. To assess baseline group differences, independent *t*-tests or Mann–Whitney U tests will be used for continuous variables, and chi-square tests or Fisher’s exact tests will be applied for categorical variables.

The analysis will adhere to an intention-to-treat (ITT) principle. The normality of the outcome variables will be evaluated using the Shapiro–Wilk test. Depending on the distribution, either parametric or non-parametric tests will be selected accordingly. To examine intervention effects, two-way repeated-measures ANOVA will be employed with group (intervention vs. control) as the between-subject factor and time (pre- and post-intervention) as the within-subject factor. Interaction effects will be interpreted to determine the differential change over time between groups. Where sphericity assumptions are violated, appropriate corrections (e.g., Greenhouse–Geisser adjustment) will be applied.

All hypothesis testing will use a two-sided α level of 0.05. Estimates of intervention effect will be accompanied by 95% confidence intervals.

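### The planned group-by-time test equals an unadjusted change-score t-test that omits the stratification factors; ANCOVA on baseline, site and functional status would be more precise at almost no cost

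*Protocol article*

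**What the plan says.** Section 2.9 names the model and its factors: "two-way repeated-measures ANOVA will be employed with group (intervention vs. control) as the between-subject factor and time (pre- and post-intervention) as the within-subject factor". It then says how the effect is read: "Interaction effects will be interpreted to determine the differential change over time between groups". No covariate is mentioned. The same section sets "All hypothesis testing will use a two-sided α level of 0.05" and promises 95% confidence intervals for the effect estimates.

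Section 2.2 fixes the number of measurements: "Outcome assessments will be conducted at two key time points: before the intervention (baseline) and after completing the 8-week program (post-intervention").

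Section 2.4 describes the allocation: "Randomization will be stratified by study site and baseline functional status, with block sizes of four to six, to minimize imbalance between groups". Section 2.3 gives the reason: "Randomization will be stratified by study site and baseline functional status to ensure that both groups have comparable distributions of key characteristics". Neither factor reappears in section 2.9.

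**The concern.** A model with group and time as its only factors makes poor use of what the trial collects. Every participant has a baseline value before randomization, yet its relation to the post value is imposed and not estimated. The design balances the arms on site and functional status. If those factors also predict change, leaving them out keeps variation in the error term that allocation has already removed from the group comparison. The standard error is then larger than it needs to be.

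The protocol itself regards these factors as relevant. Section 2.1 relies on stratification by functional status to deal with varying time since stroke, and the Discussion expects differences in functional status to affect outcomes. What is at stake is power and interval width in a trial of modest size. The validity of the test is not in question.

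**Working it through.** **The plan's own figure.** The article gives no SD, pre-post correlation or precision for this model. Its only related figure is the target of 120, from d = 0.5, α = 0.05, 80% power and 20% attrition. A two-sided two-sample t-test with those inputs needs 64 per arm, so 128 evaluable and 128/0.8 = 160 randomized. The 120 is therefore not reproduced. That is a separate matter. Here it only supplies the evaluable number: 120 × 0.8 / 2 = 48 per arm.

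**Step 1: what the interaction test is.** With two time points, the interaction contrast is the difference between arms in mean (post − pre), and the interaction F equals the square of the t statistic on change. A numerical check on simulated data gave 0.5328 for both.

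**Step 2: variance.** Let the post SD be σ, the pre SD kσ, and the pre-post correlation ρ. Per participant:
- change score: σ²(1 + k² − 2ρk), which is 2σ²(1−ρ) when k = 1
- ANCOVA on baseline: σ²(1−ρ²)

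With k = 1, the ratio of ANCOVA to change score is (1+ρ)/2, so the saving is (1−ρ)/2 of the change-score variance. Interval width shrinks by 1 − √((1+ρ)/2).

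**Step 3: power.** Take 48 per arm, two-sided α = 0.05, and an assumed difference of 0.5 post-score SD. The standardized difference is 0.5/√(2(1−ρ)) for change and 0.5/√(1−ρ²) for ANCOVA. Power comes from the noncentral t.

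| ρ (assumed) | Variance, change (σ²) | Variance, ANCOVA (σ²) | Variance saved | Width saved | Power, change | Power, ANCOVA |
|---|---|---|---|---|---|---|
| 0.3 | 1.40 | 0.91 | 35% | 19.4% | 54% | 72% |
| 0.5 | 1.00 | 0.75 | 25% | 13.4% | 68% | 80% |
| 0.7 | 0.60 | 0.51 | 15% | 7.8% | 88% | 92% |
| 0.8 | 0.40 | 0.36 | 10% | 5.1% | 97% | 98% |
| 0.9 | 0.20 | 0.19 | 5% | 2.5% | about 100% | about 100% |

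**Step 4: unequal SDs.** The excess variance of the change score over ANCOVA is (k−ρ)²σ². At ρ = 0.7:
- k = 0.7: excess 0, so no saving
- k = 0.8: 0.01/(0.51 + 0.01) = 2%
- k = 1: 0.09/(0.51 + 0.09) = 15%
- k = 1.2: 0.25/(0.51 + 0.25) = 33%

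**Step 5: the strata.** A simulation used 96 participants, four sites, two functional-status strata formed by splitting the outcome's baseline at its mean, blocks of four, and 2,500 runs per setting. Coverage of the nominal 95% interval from the planned model was:
- no site effect on change: 97.3%, 96.2%, 95.1% and 95.3% at ρ of 0.3, 0.5, 0.8 and 0.9
- site-effect SD of 0.3 on the post value: 96.7% to 97.5%

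ANCOVA with baseline and strata gave 94.5% to 95.7% throughout. Without site effects, its mean half-width at ρ = 0.3 was 0.389 against 0.479, or 1 − 0.389/0.479 = 19% narrower. At ρ = 0.8 it was 0.246 against 0.257, or 4% narrower. Both are close to the formula in step 2.

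**The case against.** The other side has several good points.

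- **Validity.** Under randomization the change-score comparison is unbiased, and leaving out balanced factors makes it conservative, not liberal. This stands in full: no false-positive risk has been shown.
- **Baseline is used.** A reader might infer that the model ignores baseline. It does not: baseline is the first level of the time factor and is subtracted. What is missing is an estimated slope.
- **The size is assumed.** No correlation is reported, and the outcomes in Table 3 are too mixed (body composition, strength, timed tests, balance scores) for one value to fit all. At ρ of 0.9 or more the saving is 5% or less. Equal SDs are also an assumption, and the entry cut-offs in section 2.1 could narrow the baseline spread. This stands, and the saving moves both ways.
- **The power gap depends on the scale of d.** The article says only that "The effect size (Cohen’s d = 0.5) was selected based on prior studies", not which SD is meant. If 0.5 is in change-score SDs, power is 68% vs 75% at ρ = 0.7 and 68% vs 72% at 0.8. ANCOVA is still ahead on that scale.
- **Stable site differences cancel on subtraction.** Only factors that predict change widen the interval needlessly. With no site effect and ρ of 0.8 to 0.9, coverage was essentially nominal.

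One might add that an article condenses its source and that a separate analysis plan could include covariates. But section 2.9 does not leave the model open. It names the factors and the term to be interpreted, so an adjusted analysis would depart from the published text.

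**Conclusion.** The point holds as a loss of precision. The identity with a change-score t-test and the absence of both stratification factors follow from the text alone. With known variances and correlation, ANCOVA's variance is never larger than that of the change score, and with equal SDs it is smaller for every ρ below 1.

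The size is conditional. With equal SDs and ρ between 0.3 and 0.9, the variance saving runs from 35% down to 5% and intervals narrow by about 19% to 3%. At 48 per arm the power gain is substantial at ρ of 0.5 or below and slight at 0.8.

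Two stronger readings are not supported. One is that the plan forfeits a known 10% to 35% of the variance reduction it could achieve. Those percentages are shares of the change-score variance, and they apply only if ρ lies between 0.8 and 0.3. The other is that a definite true test size below 5% can be stated. That needs the share of variance in change explained by the strata, which the article does not give. All that can be said is that the planned intervals are somewhat too wide wherever strata or baseline predict change.

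**What to change.** In section 2.9, replace the two-way repeated-measures ANOVA with an ANCOVA for each outcome: post value on group, the baseline value of that outcome, site (four levels) and the functional-status stratum used in randomization. Report the adjusted group difference with its 95% confidence interval as the intervention effect. The sphericity correction can then be deleted; with two time points it never applies.

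The cost is wording plus about five degrees of freedom: one for baseline, three for site, and one for functional status if it has two levels (the article does not say). With 96 evaluable participants, residual degrees of freedom fall from 94 to 89. All covariates are available before randomization, and the software already named can fit the model.

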## 3. Discussion

This multicenter randomized controlled trial aims to assess the effectiveness of a community-based HSPT program for stroke survivors with sarcopenia. While resistance training has been widely recommended as a therapeutic strategy for sarcopenia, limited evidence exists regarding the use of high-velocity training specifically designed to restore functional capacity in post-stroke populations. This study addresses this gap by delivering a power-oriented resistance program in real-world community settings, which may enhance the continuity of care from hospital-based rehabilitation to independent living [19,20].

Stroke-related sarcopenia is distinct in its manifestation, often involving asymmetrical muscle wasting, impaired neuromuscular activation, and physical inactivity [21]. These impairments affect both paretic and non-paretic limbs and contribute to significant mobility limitations. High-speed power training prioritizes rapid force production and is particularly effective for targeting type II muscle fibers—fibers known to atrophy rapidly after stroke and aging. Previous studies have shown that such training improves gait, sit-to-stand performance, and overall balance more effectively than traditional slow-velocity strength training [22,23].

Importantly, this trial incorporates a community-based delivery model across four outpatient rehabilitation centers, ensuring external validity and real-world applicability. The decentralized structure allows the intervention to be embedded in routine rehabilitation practices, improving feasibility and access for stroke survivors. Furthermore, the standardized training protocol and supervision by qualified exercise professionals contribute to the safety and reproducibility of the intervention [32,33].

A notable strength of this study is its comprehensive outcome framework, including objective measures of muscle strength, body composition, physical performance, and balance. These multidimensional assessments are essential for evaluating the multifaceted impact of sarcopenia and its treatment [34,35]. The trial ensures methodological rigor and minimizes measurement bias by employing validated instruments and consistent procedures across all study sites.

However, certain limitations should be acknowledged. The relatively short intervention duration and lack of long-term follow-up are limitations. These factors may affect the generalizability of the findings and limit our ability to assess sustainability. The intervention period is limited to 8 weeks, and longer-term outcomes remain unexplored. Additionally, due to the nature of the intervention, blinding participants is not feasible, which may introduce performance bias. Lastly, heterogeneity in baseline functional status and cognitive ability among stroke survivors may influence intervention adherence and outcomes, despite efforts to standardize implementation. The sustainability of community-based rehabilitation programs depends on the competency and availability of community healthcare workers. In our model, trained exercise specialists deliver the intervention with supervision from physical medicine and rehabilitation (PM&R) physicians. Equipment requirements are minimal and adaptable to local settings. In implementing community-based programs, practical factors such as equipment availability, exercise space, and sustainability must be considered. Future studies should also evaluate the long-term impact of HSPT on sarcopenia and mobility in real-world settings. Stroke survivors with sarcopenia often have reduced exercise tolerance and require greater supervision. Ongoing monitoring by trained community health professionals may improve adherence and maximize intervention outcomes. Future implementation should consider strategies for regular supervision, continued training, and system integration into public health frameworks. Supportive policies, dedicated funding, and infrastructure are also essential to ensure the sustainability and scalable implementation of these programs across communities. Nevertheless, this study is expected to contribute valuable evidence regarding the role of HSPT in stroke rehabilitation, particularly in managing post-stroke sarcopenia. Its findings may inform clinical practice and guide the future development of community-integrated rehabilitation models for improving functional recovery and long-term health in this population.

## 4. Conclusions

This multicenter randomized controlled trial is designed to investigate the effects of a community-based high-speed power training (HSPT) program for stroke survivors with sarcopenia. By targeting neuromuscular deficits specific to post-stroke sarcopenia and implementing a structured, progressive intervention in real-world settings, this study aims to bridge the gap between hospital-based rehabilitation and long-term functional independence.

The proposed program incorporates principles of power training known to enhance muscle strength, mobility, and balance, which are critical for reducing fall risk and promoting community reintegration in stroke populations. Moreover, the inclusion of objective and multidimensional outcome measures strengthens the methodological rigor and clinical relevance of the findings.

This trial is expected to contribute valuable evidence supporting the feasibility and effectiveness of HSPT in community settings. The results may inform rehabilitation protocols and public health strategies for improving long-term outcomes among stroke survivors with sarcopenia. A key limitation of this study is the relatively short duration of the intervention (8 weeks), which may be insufficient to observe sustained functional gains or long-term adherence. Additionally, the absence of follow-up assessments limits our ability to evaluate the durability of treatment effects. Future studies should incorporate extended follow-up periods (e.g., 6–12 months) to assess the maintenance of functional improvements and long-term community reintegration. Ultimately, this study seeks to promote a sustainable model of community-based rehabilitation that addresses the persistent functional limitations and health risks faced by this vulnerable population.

## Figures and Tables

**Figure 1 life-15-00748-f001:**
[figure not shown]
Study flowchart.

**Table 1 life-15-00748-t001:** Structure of the program.

Category		Contents
Warm-Up Cool-Down	Aerobic	Walking
	Flexibility	Static/Dynamic Stretching
Main Exercise Resistance Training	Lower Extremities	Squat, Lunge, Bridge
	Trunk	Deadlift, Leg Raise, Russian Twist, Crunch, Reverse Crunch, Side Crunch, Sit-up, Back Extension, Superman Position
	Upper Extremities	Shoulder Press, Biceps Curl, Triceps Extension, Chest Press, Back Row

**Table 2 life-15-00748-t002:** Baseline Clinical Profile and Physical Measurements of Participants.

Category	Variables	Units/Response Options
Clinical Profile	Chronological age	Age in years
	Biological sex	Sex (M/F)
	Classification of stroke	Stroke subtype
	Presence of comorbidities: hypertension, anemia, respiratory disorders, orthostatic hypotension, diabetes, cardiovascular disease, coronary interventions, epilepsy, psychiatric medications (e.g., antidepressants), recent lower back pain (within 4 weeks), joint pain affecting mobility, osteoporosis, and fracture history (spine, hip, or femur due to falls or bone fragility)	Confirmed or not
Physical Measurements	Systolic and diastolic	mmHg
	Stature	Height in centimeters
	Body weight	Weight in kilograms
	Body mass index	BMI category
	Days since hospital discharge	Elapsed time in days

**Table 3 life-15-00748-t003:** Outcome domains and assessment tools.

Outcome Domain	Assessment Tool
Muscle Strength	Handgrip Strength (Hand Dynamometer) Isokinetic Strength Test
Body Composition	Dual-Energy X-Ray Absorptiometry (DXA) Bioelectrical Impedance Analysis (BIA)
Physical Performance	Short Physical Performance Battery (SPPB)
Static Balance	Berg Balance Scale (BBS)
Dynamic Balance and Gait	Timed Up and Go Test (TUG) 10-Meter Walk Test (10MWT)

